## Abstract

**Background:**

Tooth decay is the most common chronic disease of childhood in the world. Many children develop caries early in their lives, and go on to develop further caries and sepsis as they grow up, indicating failure in prevention. As a result, many end up requiring general anaesthesia to undergo treatment for a disease that is completely preventable. Previous studies have suggested that the families of these children need better oral health education as well as better support in implementing healthy practices at home, as they feel impeded by broader life challenges. Parents of these children have suggested utilizing modern technologies, such as the internet, DVDs and video games as methods of delivery of education that might fit in with their busy lifestyles. The aim of this investigation is to assess the acceptability and efficiency of an oral health education video game directed at these children and their families.

**Methods/Design:**

A two-armed phase-II randomized controlled trial will assess a children’s oral health education video game in comparison with verbal oral health education in terms of: family satisfaction, effect on oral health knowledge, and effect on dietary and oral hygiene habits. Up to 110 four- to ten-year-old children, referred for tooth extraction under general anaesthesia due to caries, will be recruited. A sample of 45 participants in each group will be needed to provide 80 % statistical power. The primary outcome measures for this study are: (1) parent and child satisfaction with the intervention, as indicated using a visual analogue scale; (2) improvement in the child’s dietary knowledge measured by a pictorial dietary quiz; and (3) changes in the child’s diet and oral hygiene habits, measured using a children’s dietary questionnaire completed by the parent, and snacking and toothbrushing diaries completed by the child. Measures will be taken at baseline, directly after the intervention, and three months later.

**Discussion:**

This study is a phase-II randomized controlled trial of an oral health education video game for high caries risk children and their families. Few protocols such as this are available in this much-needed research area.

**Trial registration:**

ISRCTN94617251.

## Background

Tooth decay is the most common childhood illness in the world [1]. Early childhood caries is commonly defined as the occurrence of any sign of dental caries on any tooth surface before the age of 6 years [2]. In England, 12 % of children aged three [3], and 28 % of children aged five, have dental caries [4]. The disease can gravely affect the quality of life of these children and their families [5]; furthermore, contracting the disease at an early age puts these children at greater risk of developing caries and sepsis in the future [6, 7]. For a significant proportion, the end result is dental extraction under general anaesthesia, which nowadays is the most common reason for hospital admission in children aged five to nine years in England [8]. Reported general anaesthesia repeat rates are fairly high (25 %), despite rigorous examination and radical treatment [9]. Moreover, many of these children have siblings who have had similar treatment [10]. These findings suggest that there is failure in improving caries prevention in those children and their families postoperatively. Indeed, almost 80 % of parents of these children requested more support in preventing dental caries in their children. Furthermore, 55 % requested that more help with caries prevention be included in subsequent hospital visits [10].

Previous studies suggested that these families display poor oral health knowledge as well as face difficulties in implementing healthy oral habits at home [11]. Given the suggested deficiency in oral health knowledge in these families, provision of oral health advice can be an important part of promoting oral health, and exploration of methods of advice delivery that are effective and acceptable to them is necessary. In a previous study, parents of children referred for extractions under general anaesthesia suggested that different methods for delivering oral health advice can be acceptable, including: websites (64 %), leaflets (63 %), and DVDs (49 %) [10]. In another study, similar findings were reported: (89 %) found leaflets and (67 %) found the internet acceptable methods for oral health advice delivery [12].

The use of video games is a less traditional method of oral health advice that should be considered and explored, as these games might have great potential. Evidence suggests that such games have several advantages over other methods of learning, including: multisensory support, problem-based learning, activation of prior knowledge, immediate feedback, and provision of a social environment involving communities of players [13]. Moreover, video gaming is widely practised nowadays, especially by children. Almost 90 % of American children and teens were reported to play such games on various platforms [14], with the average child aged eight to ten years spending an hour per day playing [15]. In the UK, more than 90 % of six- to nine-year old boys and girls are reported to play such games [16].

Health researchers have realised the potential games may have in delivering health advice. Previous research suggests that using such games to promote a healthy diet carries potential. For example, a study that used a game to promote intake of fruits and vegetables has reported that children had one more serving of fruit or vegetable per day after the intervention and that those with the lowest intake at the baseline benefited the most [17]. Another study assessed the effectiveness of a nutritional education computer package [18] in 8- to 11-year olds in schools compared with traditional methods and suggested that both methods increased the children’s knowledge and that knowledge was retained three months later [19]. A review in 2008 that included 25 studies utilizing such games concluded that they can induce positive health-related outcomes [20]. A more recent review has suggested that amongst 38 studies and a total of 195 health outcomes, video games improved 69 % of psychological therapy outcomes, 59 % of physical therapy outcomes, 50 % of physical activity outcomes, 42 % of health education outcomes, 42 % of pain distraction outcomes, and 37 % of disease self-management outcomes [21]. The reviews also revealed that although these games show the potential to improve health outcomes, most studies are of poor quality and more rigorous randomized controlled trials are needed.

Evidence of the use of video games in oral health education in particular is scarce. A pilot study involving 26 four-year-old nursery children tested a prototype oral health education video game developed by one of the investigators (MTH) and an MSc computer science student [22]. The results suggested no difference in healthy food identification after using the video game, although the sample size was too small to reach significance. Teachers involved in the study viewed the game positively but recommended that it involve more interaction and additional material [23].

In 2008, two of the authors (CR) and (MTH) developed a new prototype oral health education video game. The development process comprised of three steps: first, collection of opinion from experts in the fields of paediatric dentistry, dental public health, nutrition and child education to inform the game’s design. Second, designing the game using the aforementioned input and using Microsoft PowerPoint, and finally, assessment by six six-year-old children to test functionality, child engagement and navigation. The game was named ‘Barney’s healthy foods’, and included an avatar to guide the child through it, as this has been suggested to improve the learning experience [24]. The game was also developed in line with the Scottish National Curriculum, as oral health education programmes that are well integrated into the National Curriculum have been suggested to lead to improvements in children’s oral health knowledge [25]. The game was assessed in a phase-I randomized controlled trial (RCT) that included four- to seven-year-old children in two primary schools in Stornoway, Scotland. The results suggested that this method of oral health education delivery can be as effective as regular paper-based methods in improving children’s recognition of healthy foods [26].

In light of those findings, the current study is a phase-II blind RCT that aims to assess an oral health education video game in comparison with verbal oral health education in terms of family satisfaction, effect on oral health knowledge, and effect on dietary and oral hygiene habits in high caries risk families.

### Aims

#### Primary aim

The primary aims of this study are: (i) to assess the satisfaction of high caries risk children and their parents with delivery of oral health education through an interactive video game, and (ii) to assess the game’s potential to improve the child’s oral health knowledge and dietary and oral hygiene practices.

#### Secondary aim

The secondary aim of this study is to establish proof of concept for the use of interactive video games in delivering oral health education for children.

### Research questions

Would an oral health education video game be an acceptable method to deliver oral health prevention information to high caries risk children and their families? Can the use of such an intervention improve their oral health knowledge and would that improvement be reflected in their oral health practices at home?

### Null hypothesis

The use of a video game to deliver oral health education to children is neither as acceptable nor as effective in improving the child’s oral health knowledge and practices as verbal education delivered by an extended dental nurse or trained health promoter.

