#### Sample size

The primary outcome measure in this study is user satisfaction with the intervention, assessed using a visual analogue scale. This is constructed as a continuous 100 mm line, with a score at the 0 mm mark indicating complete dissatisfaction with the intervention and a score at the 100 mm indicating complete satisfaction. As far as we know, this is the first study measuring patient’s satisfaction with the use of video games for oral health education. Assuming that our population will have a standard deviation of 25 mm, which is similar to patient satisfaction measured in studies in other fields [29], and aiming to detect a difference of at least 15 mm between the groups to indicate its clinical significance, a sample of 45 participants in each group will be needed to provide 80 % power, at the 5 % significance level, to detect effects of size 0.6 and above. This number of participants is also sufficient based on our calculations using the results of the pictorial dietary quiz used in the phase-I RCT. Anticipating a 20 % dropout rate [30], we intend to recruit approximately 108 participants.

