#### Statistical analysis

Descriptive statistics for all explanatory variables at baseline will be provided, overall and by study group. Analysis of variance and chi-square tests will be used to highlight any significant imbalance between groups.

Student’s *t* test will be used to compare the two groups’ parent and child visual analogue scale scores, indicating satisfaction with intervention. It will also be used to compare children’s dietary questionnaire, toothbrushing scores, and healthy snack selection scores. Since the children’s pictorial dietary quiz is the only measure taken at three points (baseline, directly after intervention, and three months later), its scores will be analysed using linear multivariate regression.

Verbal feedback provided by parents and children on intervention will be written down verbatim and will be analysed using simple content analysis.

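### The null hypothesis is worded as inferiority of the game, but the trial is sized and analysed to detect a difference, so a non-significant result can neither reject that null nor support parity with verbal education

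*Protocol article*

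**What the plan says.** Three sections of the protocol article bear on this.

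- **Null hypothesis.** The game is "neither as acceptable nor as effective in improving the child’s oral health knowledge and practices as verbal education" given by a dental nurse or health promoter. This one sentence covers acceptability, knowledge and practices.
- **Sample size.** "The primary outcome measure in this study is user satisfaction with the intervention, assessed using a visual analogue scale". The calculation is described as "aiming to detect a difference of at least 15 mm between the groups to indicate its clinical significance". The other inputs are "Assuming that our population will have a standard deviation of 25 mm" and "80 % power, at the 5 % significance level", "to detect effects of size 0.6 and above", and the result is that "a sample of 45 participants in each group will be needed".
- **Statistical analysis.** Student's t test "will be used to compare the two groups’ parent and child visual analogue scale scores, indicating satisfaction with intervention". The same test is planned for the dietary questionnaire, toothbrushing scores and snack scores. The pictorial quiz is to be analysed by regression.

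No non-inferiority or equivalence margin is given in any section, and no rule based on a confidence interval. The sidedness of the 5% level is not stated.

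**The concern.** A null hypothesis is the statement that the test is built to reject. Rejecting the one written here would show that the game is at least as acceptable or as effective as verbal education. That is a non-inferiority claim and needs a margin. The null of a t test is that the means are equal. The two do not correspond:

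- A non-significant t test leaves the written null standing, although a reader could easily take it as showing the game to be as acceptable as the nurse's advice.
- A t test significantly favouring verbal education rejects the tested null while agreeing with the written one.
- The sentence joins several outcomes. Read literally, it is false as soon as one component holds, yet the outcomes are analysed separately and nothing says which must succeed.

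What is at stake is the conclusion the trial may draw. The Background already describes the phase-I result in terms of the game matching paper-based methods. The Discussion recognises that participants may score the nurse-delivered control more generously. A moderate deficit for the game on the satisfaction scale is therefore a realistic result, and the plan should not leave room for it to be reported as parity.

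**Working it through.** **Inputs** (Sample size section): difference 15 mm, standard deviation 25 mm, standardised effect 15/25 = 0.6, 80% power, 5% level, 45 per arm.

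**1. Which test was the trial sized for?**
- Two-sided, normal approximation: n = 2 × (1.960 + 0.842)² × (25/15)² = 43.6, so 44 per arm. The exact t-test calculation gives 44.6, so 45, with power 80.4% at 45 per arm. The plan's figure is reproduced.
- One-sided 5%: n = 2 × (1.645 + 0.842)² × (25/15)² = 34.3, so 35. This does not match.

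So 45 per arm is a two-sided test-of-difference calculation. It agrees with the planned t test but not with the null hypothesis as worded.

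**2. What can a non-significant result exclude?**
- Standard error = 25 × √(2/45) = 5.27 mm.
- 95% half-width = t(0.975, 88 df) × 5.27 = 1.987 × 5.27 = 10.5 mm.
- An observed deficit for the game just under 10.5 mm is non-significant, with a lower confidence limit near −21 mm.
- 15 − 10.5 = 4.5, so any observed deficit between about 4.5 and 10.5 mm is non-significant yet does not exclude a true deficit of 15 mm, the difference the plan ties to clinical significance.

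**3. How often is the test non-significant when the game is truly worse?** (two-sided t test, 45 per arm, standard deviation 25 mm)

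| True deficit | Power | Non-significant |
|---|---|---|
| 5 mm | 15.5% | 84% |
| 10 mm | 46.7% | 53% |
| 15 mm | 80.4% | 20% |

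If all 108 recruits (54 per arm) gave a satisfaction score, the half-width would be 1.983 × 25 × √(2/54) = 9.5 mm, and the first two non-significance rates would be 82% and 46%. The picture is the same.

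**4. What would a non-inferiority test need?** The protocol states no margin, so a range M is assumed, with true difference 0 and one-sided 2.5%. Sample size per arm for 80% power is 2 × (1.960 + 0.842)² × (25/M)². Power at 45 per arm is Φ(M/5.27 − 1.960).

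| Assumed margin | n per arm for 80% power | Power at 45 per arm |
|---|---|---|
| 15 mm | 44 | 81% |
| 12.5 mm | 63 | 66% |
| 10 mm | 99 | 48% |
| 5 mm | 393 | 16% |

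The present size fits only the 15 mm margin. Under that margin, parity could be claimed whenever the observed difference (game minus verbal) exceeded about −4.5 mm. That would happen in about 15% of trials if the game were truly 10 mm worse, and in about 46% if it were 5 mm worse.

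**The case against.** The strongest reply is that the operative design is coherent. The sample size and the t test agree with each other, and the outlier is one loosely worded sentence. This is a phase-II trial with a proof-of-concept secondary aim. The aims and research questions ask whether the game is acceptable and can improve knowledge and habits; they do not promise parity. The outcomes are listed and analysed separately, which limits the harm of the joint wording. How non-significant results are reported may be left to an analysis plan that is not shown.

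Much of this stands, and it is why the remedy is mainly rewording. It does not remove the contradiction, because the protocol itself labels that sentence its null hypothesis and the planned test has a different one.

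Three stronger readings are tempting, and the document does not support them.

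- *No planned result could support the game being as acceptable as verbal education.* This goes too far. A t test significantly favouring the game excludes inferiority on that outcome.
- *The authors intend to report non-significance as parity.* Nothing says so. The parity wording in the Background concerns the phase-I trial. The fault is that the plan leaves the route open.
- *The plan's 15 mm can serve as the margin, so a non-inferiority test costs nothing.* The arithmetic works, but the protocol uses 15 mm to mark clinical significance. A margin of that size would tolerate a deficit of almost that amount.

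**Conclusion.** The null hypothesis is wrong for the planned test. It asserts inferiority of the game jointly over acceptability, knowledge and practices, while the trial is sized and analysed for a two-sided difference with no margin. As planned, only a result significantly favouring the game excludes inferiority, and only on the outcome tested. A non-significant result supports neither parity nor rejection of the written null.

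The satisfaction figures rest on the protocol's standard deviation of 25 mm, 45 analysed per arm and a two-sided 5% level. The two-sided level is inferred because only that reproduces 45. The margins other than 15 mm are assumptions. The article gives no inputs for the same calculation on the quiz, questionnaire or diaries; for those the mismatch is one of logic only.

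**What to change.** 1. Restate the null hypothesis as no difference between arms, separately for parent satisfaction, child satisfaction, the pictorial quiz, the dietary questionnaire, and the toothbrushing and snack diaries.
2. In the Statistical analysis section, say that each between-arm difference will be reported with its 95% confidence interval, and that a non-significant result is inconclusive and will not be reported as the game being as acceptable or as effective as verbal education.
3. Do not adopt 15 mm as a non-inferiority margin. If parity is the aim, pre-specify and justify a smaller margin for each outcome on which it will be claimed, say whether parent and child satisfaction must both meet it, and add the confidence-interval rule. Either re-size the trial or state the lower power at 45 per arm: for satisfaction, about 66% at 12.5 mm and 48% at 10 mm, assuming a true difference of 0.

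Items 1 and 2 cost a few sentences and no participants or data. Item 3 has a real cost if the trial is re-sized: 63 per arm at 12.5 mm or 99 at 10 mm, before dropout. The Trial status section says recruitment is ongoing, so the wording should be settled before the randomisation code is broken.

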## Methods

### Modification of video-game prototype used in phase-I RCT

In preparation for the phase-II RCT, a few modifications of the prototype video game used in the phase-I RCT were necessary. The aim was to update the game in light of the results of the phase-I RCT, newly available technology, dietary guidelines, and the population to be targeted in the phase-II RCT.

The research team updated the game content, including the addition of a segment that includes advice on the consumption of fruit juice and another that includes advice on fluoride, as previous findings by the authors have suggested that this cohort of children and their parents received little advice on those two issues [11]. In addition, the game’s graphics were updated, including the introduction of a new avatar (Fluffy the hamster). CrazyTalk7 was used to develop the new avatar, and a new voiceover was recorded and used. Fig. 1 is an example of these updates. Finally, the game’s software was updated to HTML5 (software automatically installed on every computer, Smartphone or tablet) and the game was installed on a tablet (iPad), because they are more popular amongst children [27], can make the gaming experience easier and more interesting [28], and allow for easier set-up in the research location.

**Fig. 1 Fig1:**
[figure not shown]
Video-game modification

Once these modifications were introduced, the researcher (AA) ran the game numerous times to ensure it ran smoothly without any technical difficulties. The game was then further tested by a user group within the pilot study.

### Pilot study

The pilot study aimed to: (i) assess user group interaction with the updated video game and notice any technical difficulties, (ii) assess feasibility of the main study protocol; (iii) assess blinding and randomization methods; and (iv) familiarize all members of the research team with the standard operating procedure.

The pilot study followed the same design, recruitment criteria and methods as the planned phase-II RCT. However, the introduction of blinding and randomization was gradual, so that the research team could be familiarized with the process. Data collection took place in May and June 2013.

Ten participants were recruited. Technical difficulties faced by the users during playing the video game were noted and corrected by the researcher (AA). In addition, the optimum physical setting for the study was determined and the team responsible for the day-to-day operations of the RCT (researcher (AA) and two trained dental nurses, both of whom had a health promotion qualification) became familiar with the recruitment, randomization and blinding processes.

### Phase-II randomized controlled trial protocol

#### Methods and design

This study will be a two-armed blind RCT that will recruit children referred for dental extractions under general anaesthesia, as well as their parents. The participants will be randomized into two groups. In the study group, the child and escort will undergo self-directed ‘play’ about oral health using the video game on an iPad and receive a copy on a DVD to run it on a home personal computer. In the control group, the child and escort will receive verbal oral health advice from a dental nurse who has a health promotion qualification.

The participants will be recruited at the medical pre-assessment clinic at the day surgery unit at King’s College Hospital in London. All children scheduled for a procedure under general anaesthesia attend this clinic approximately two weeks prior to their surgery for a medical evaluation of fitness to undergo general anaesthesia.

